### Randomisation

Those patients who consent to take part in the trial will be randomised in a 1:1 allocation to TKA or PFA. The randomisation sequence will be computer generated. An independent researcher will phone the secure centralised, telephone randomisation service. The treatment allocation will then be emailed to the medical secretary of the operating consultant by the randomisation service. The medical secretary will then enter the allocation on to the patient's operation booking form. This will ensure that the research associates collecting outcome data remain blind to the treatment allocation,

### Blinding

The patients will also be blind to their treatment allocation to allow for an unbiased comparison to be made between the two interventions. The surgeons will, of course, not be blind to the treatment but will take no part in the post-operative assessment of the patients.

### Statistical analysis

Standard statistical summaries (e.g. medians and ranges or means and variances, dependent on the assumed distribution of the outcomes) and graphical plots showing correlations will be presented for the primary outcome measure (WOMAC) and the secondary outcome measures. Baseline data will be summarized to check comparability between treatment arms, and to highlight any characteristic differences between those individuals in the study, those ineligible, and those eligible but withholding consent. The main analysis will investigate differences in the primary outcome measure, the WOMAC score, between the two treatment groups on an intention-to-treat basis at 12 months post-operation. The significance in responses between treatment groups will be formally assessed using an independent samples *t*-test; based on an assumed approximate normal distribution for this outcome measure. Tests will be two-sided and considered to provide evidence for a significant difference if p-values are less than 0.05 (5% significance level). Estimates of treatment effects will be presented with 95% confidence intervals. A linear regression analysis will also be undertaken that will incorporate terms that model the effects of patient age and gender in addition to the effects of the treatment groups (TKA and PFA). Results from the unadjusted and adjusted analyses will be presented graphically, together with diagnostic plots that check the underlying model assumptions. Depending on the nature of the data, various derived variables (e.g. logarithmic transformations of scores) may be created and analysed, in addition to the primary outcome. Although missing data is not expected to be a problem for this study, the nature and pattern of the missingness will be carefully considered -- including in particular whether data can be treated as missing completely at random (MCAR). If judged appropriate, missing data will be imputed, probably using the multiple imputation facilities available in R http://www.r-project.org/. A detailed statistical analysis plan (SAP) will be agreed with the Data Management Committee (DMC) at the start of the study. Any subsequent amendments to this initial SAP will be clearly stated and justified. Interim analyses will be performed only where directed by the DMC. The routine statistical analysis will be carried out using R http://www.r-project.org/.

This trial is expected to deliver results in early 2013.

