**Methods/design:**

Patients who are deemed suitable, by an Orthopaedic Consultant, for patellofemoral arthroplasty and medically fit for surgery are eligible to take part in this trial. The consenting patients will be randomised in a 1:1 allocation to a total knee or patellofemoral arthroplasty. The randomisation sequence will be computer generated and administered by a central independent randomisation service. Following consent, all participants will have their knee function, quality of life and physical activity level assessed through questionnaires. The assigned surgery will then be performed using the preferred technique and implant of the operating surgeon. The first post-operative assessments will take place at six weeks, followed by further assessments at 3, 6 and 12 months. At each assessment time point all complications will be recorded. In addition, community and social care services usage will be collected using a patient questionnaire at 3, 6 & 12 months. The patients will then be sent an annual postal questionnaire. The questionnaire will ask about any problems, knee pain and function following their knee arthroplasty to monitor long-term function and failure rates.

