### Sample size

Previous work has suggested that the WOMAC score is the most sensitive condition-specific tool for assessing interventions in knee osteoarthritis [12,18]. Angst et al. [19] successfully demonstrated the use of the 17-item functional section of the WOMAC score to determine sample size.

The sample size calculation was based on a two-arm parallel group design and an assumed approximate normal distribution for the primary outcome measure (WOMAC). The required number of patients in each arm of the trial is 29, based on an independent samples *t*-test and an assumed population standard deviation of 10.8 points [20] and a minimum clinically important difference of 8 points [19]; this gives a relatively large standard effect size of 0.74. The proposed number of patients will provide 80% power to detect a difference at the 5% level (PS, Power and Sample Size Calculation Software version 2.1 30th February 2003, available at http://biostat.mc.vanderbilt.edu/wiki/Main/PowerSampleSize). To allow for a 10% loss to follow-up we will aim to recruit 32 patients in each arm, giving a total of 64 patients.

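### Neither the primary t-test nor the named regression adjusts 12-month WOMAC for the baseline knee function the trial already collects, giving up precision and protection from chance imbalance

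*Protocol article*

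**What the plan says.** - **Primary test.** Under Statistical analysis, the WOMAC is compared "between the two treatment groups on an intention-to-treat basis at 12 months post-operation". The comparison is "formally assessed using an independent samples *t*-test; based on an assumed approximate normal distribution for this outcome measure".
- **Adjusted model.** The same section continues: "A linear regression analysis will also be undertaken that will incorporate terms that model the effects of patient age and gender", in addition to treatment group. No baseline score is named.
- **Use of baseline data.** "Baseline data will be summarized to check comparability between treatment arms", and also to compare participants with ineligible and non-consenting patients. Both uses are descriptive.
- **What is collected before surgery.** The Abstract (Methods/design) says: "Following consent, all participants will have their knee function, quality of life and physical activity level assessed through questionnaires". The assigned operation follows.
- **Sizing.** Under Sample size, the trial rests on the same unadjusted t-test: SD 10.8, difference 8 points, 29 per arm, raised to 32 per arm (64 in total) for 10% loss. "The proposed number of patients will provide 80% power to detect a difference at the 5% level".
- **Allocation.** Randomisation describes a computer-generated 1:1 sequence and names no stratification factor.

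**The concern.** A patient's knee score before surgery is a natural candidate to predict the same kind of score a year later. The trial collects it and then leaves it out of both named analyses. Two things follow.

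First, the t-test keeps in its error term all the outcome variance that the baseline score could explain. In a trial of 64 patients, planned to have just about 80% power for a standardised effect of 0.74, that precision is worth having.

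Second, no stratification is described and the arms are small, so chance differences in baseline function are to be expected. A fraction r of any standardised imbalance passes into the raw 12-month difference. A comparability table can show such an imbalance but cannot correct for it, and an adjustment chosen after seeing the table would be post hoc.

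**Working it through.** **Inputs from the protocol article.** Sample size: difference 8 points, SD 10.8, 29 per arm after loss, 32 per arm recruited. Statistical analysis: two-sided 5% level.

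**Assumption.** The documents give no correlation r between baseline and 12-month WOMAC. A range is shown.

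**1. The plan's own figure.** By the normal approximation,

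n per arm = 2 × [10.8 × (1.960 + 0.842) / 8]² = 28.6, rounded up to 29.

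Power at 29 per arm is 80.5% by this approximation and 79.2% by the exact noncentral t. The stated 29 and 80% reproduce.

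**2. Power with baseline adjustment.** The residual SD is 10.8 × √(1 − r²). Exact noncentral-t power is taken at 29 per arm, with one degree of freedom spent on the covariate. The equivalent unadjusted sample is 29 / (1 − r²).

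| r | Residual SD | Power | Equivalent unadjusted n per arm |
|---|---|---|---|
| 0 (t-test) | 10.80 | 79.2% | 29.0 |
| 0.1 | 10.75 | 79.5% | 29.3 |
| 0.2 | 10.58 | 80.7% | 30.2 |
| 0.3 | 10.30 | 82.8% | 31.9 |
| 0.4 | 9.90 | 85.6% | 34.5 |
| 0.5 | 9.35 | 89.2% | 38.7 |
| 0.7 | 7.71 | 97.3% | 56.9 |

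These figures ignore the small average variance penalty for estimating the covariate slope, about 1/(2n − 4) = 1/54 = 1.9%. Including it lowers power to 78.8% at r = 0.1, 80.0% at r = 0.2, 82.1% at r = 0.3 and 88.7% at r = 0.5. The picture does not change, but any gain at r of 0.2 or less is negligible.

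**3. Chance imbalance at randomisation.** With 32 per arm, the standard error of a baseline difference is √(2/32) = 0.25 SD. A gap of at least 0.25 SD (1 SE) arises in about 32% of randomisations, and one of at least 0.5 SD (2 SE) in about 5%.

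Shift in the unadjusted 12-month difference = r × imbalance in SD units × 10.8:

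| Imbalance | r = 0.3 | r = 0.5 |
|---|---|---|
| 0.25 SD | 0.3 × 0.25 × 10.8 = 0.8 points | 0.5 × 0.25 × 10.8 = 1.35 points |
| 0.5 SD | 0.3 × 0.5 × 10.8 = 1.6 points | 0.5 × 0.5 × 10.8 = 2.7 points |

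The largest of these, 2.7 points, is about a third of the 8-point difference (2.7 / 8 = 0.34).

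**4. Error rate given an imbalance.** Take a baseline gap of z = 1.96 SE and no treatment effect. The t statistic then has approximate mean 1.96r and variance 1 − r². The chance that it falls outside ±1.96 is about 8% at r = 0.3 and 13% at r = 0.5. Averaged over all randomisations it is 5%.

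**The case against.** The planned analysis is sound and consistent: the trial is sized and analysed by the same t-test, which is unbiased and holds its 5% error over all randomisations. The planned confidence interval already allows for chance imbalance. The documents contain no contradiction here. That all stands, so the point is about efficiency and robustness to the allocation obtained, not validity.

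The size depends on an r that the documents do not give. At r = 0.3 or below the power gain is under 4 percentage points, which also stands. The 0.5 SD imbalance is a 2-SE event, and the more ordinary 1-SE gap shifts the estimate by only 0.8 to 1.35 points. If loss to follow-up stays below 10%, more than 29 per arm will be analysed: exact power for the t-test is 80.5% at 30 per arm and 83.1% at 32.

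The regression sentence does not say that age and gender are the only terms, and the article promises a detailed SAP, which is not shown and might add a baseline score. That could change the secondary model. It does not alter the primary test, which the article fixes as unadjusted.

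Finally, the Abstract speaks of knee function by questionnaire without naming WOMAC, and Outcome measures lists more than one knee score. Baseline WOMAC is a reasonable inference, but it needs confirming.

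**Conclusion.** The concern holds. As published, the primary test is unadjusted, the regression names age, gender and treatment, and the baseline knee score is used only descriptively. The t-test is valid and meets its stated power to within rounding, so the loss is precision forgone.

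If r is 0.3 to 0.5, that is roughly 4 to 10 percentage points of power at 29 per arm, or the equivalent of 3 to 10 further patients per arm. It is negligible at r of 0.2 or less and larger above 0.5. Adjustment would also remove most of the effect of a chance baseline gap, which at r = 0.5 amounts to 1.35 points for a 1-SE gap and 2.7 points for a 2-SE gap.

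These sizes rest on the planning SD of 10.8, a linear relation between baseline and outcome, and the assumed r. The change should be made because it costs almost nothing, but the trial does not fail without it.

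**What to change.** Before unblinding, specify the primary analysis as a linear model of 12-month WOMAC on treatment group and baseline WOMAC, with age and gender included if wanted. Report the adjusted difference, its 95% confidence interval and p-value as the main result, and keep the unadjusted t-test as a supporting analysis. Treat each secondary score in the same way with its own baseline value where one is collected. State explicitly that WOMAC is completed at baseline. If the SAP already contains this model, align the protocol text with it.

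The cost is one sentence in the protocol and the SAP and one degree of freedom for the baseline term. The target of 64 patients need not change, and no new data are needed as long as WOMAC is among the baseline questionnaires.

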## Abbreviations

PFA: Patellofemoral Arthroplasty; TKA: Total Knee Arthroplasty; WOMAC: Western Ontario and McMaster Universities Osteoarthritis Index Score.
